### Questionnaires

Questionnaires on pain (VNS), functionality (ODI), and quality of life (EQ-5D) will be given at recruitment as well as at 1, 3, and 6 months postoperatively. A professional who is not involved in the study will collect all questionaires. Follow-up clinical visits will be carried out at 1, 3, and 6 months postoperatively, with acceptance deviation of 7, 14, and 21 days, respectively.

### Imaging studies

Imaging studies include 1.5 T magnetic resonance imaging. The tests must be dated no later than 6 months prior to the participant’s inclusion in the study. Any of the following changes will be considered disc degeneration: disc protrusion, extrusion, or sequestration; reduced disc intensity; annular ruptures; Schmorl’s nodes (Depressions on the surface of the vertebral bodies identified on MRI scans that result from the pressure exerted by the intervertebral discs on the endplates, causing intervertebral disc tissue herniation and displacement into the adjacent vertebral bodies); Modic changes; and/or loss of disc height.

### Modic changes

The presence of Modic type 1 changes will be considered in the evaluation of magnetic resonance images. This change is characterized by the presence of a high signal on T2-weighted sequences, with reduced signal on T1-weighted sequences [1, 2]. The frequency of Modic type 1 changes in the participants will be calculated for each of the research groups (presence or absence of colonization) and for the total number of discs analyzed in the laboratory.

### Pfirrmann classification

Degenerative changes identified in the discs will be categorized according to the Pfirrmann classification [58] using T2-weighted magnetic resonance images.

### Confounding variables

As some of this information may change during the study, the data obtained at the time of inclusion in the study will be considered. Below are the confounding variables to be analyzed:

AgeSexEducationLeave of absenceAlcohol consumption
None or sporadically (< 1 dose/day)Mild (1–2 doses/day)Moderate/High (≥ 3 doses/day)Smoking
Non-smokerSmokerEx-smokerBody mass index
Underweight (< 18.5 Kg/m^2^)Normal (18.5–25 Kg/m^2^)Overweight (25–30 Kg/m^2^)Obese (> 30 Kg/m^2^)Physical activity practice
Sedentary (not performing physical activity for at least 10 continuous minutes during the week)Active (vigorous activities for three or more days/week and for 20 min or more per session; or moderate activity or walking for five or more days/week and for 30 min or more per session; or any activity added together 5 or more days/week and 150 min or more/week)Very active (vigorous activity for five or more days/week and 30 min or more per session; vigorous activity for three or more days/week and 20 min or more per session, more moderate activity and/or walking for five or more days/week and for 30 min or more per session)Use of oral steroids up to 3 months before surgeryDiabetes

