### Patient and public involvement

Participant eligibility will be evaluated by the study researchers through a clinical interview and imaging exams evaluation, according to the participants’ interest and availability to participate in the study. If the patient agrees to take part in the study, the predetermined selection criteria will be used to evaluate them. The researchers will explain the details of the study and conduct a joint reading of the ICF. Questions about the study objectives, risks and benefits, stages, and research confidentiality will be answered. A patient will only participate upon signing the ICF at this stage of the research. A copy of this document will be given to the participant, another to the responsible researcher, and a third will be attached to the medical record. After signing the consent form, the patient will undergo an evaluation for demographic and clinical data collection and the forms developed for this purpose will be completed. If the patient is unable to read and sign the written consent form, researchers will verbally explain the study details and the patient will orally provide consent in the presence of a witness who will sign the consent form. The recruitment of participants will take place over a 6-month period, until 120 individuals are included, aiming at a minimum number of 96 collections.

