## Statistical planning

### Sample size calculation

Considering the main outcome proposed, the identification of disc colonization by *C*. *acnes*, the minimum sample size (*n*) for the population of interest will be 96 participants, according to the calculation described by Medronho et al., [59] using a confidence interval of 95% and a maximum margin of error of 10%.

The ideal sample size for analysis of secondary outcomes will depend on the incidence of the main outcome. If it is too low, an increase in the number of patients included will be performed with the inclusion of more blocks of participants. In order to have a more accurate dimension, the sample size calculation will be revised as soon as we reach half of the initially planned sample size.

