### Statistical analysis methodology

The database will be analyzed using the SPSS software, version 22.0, and R software, version 4.0.2. Descriptive analysis will be performed by charts and descriptive statistics. The inferential analysis will consider a maximum significance level of 5%. The chi-square test or Fisher’s exact test will be used for inferential analysis of the distributions of categorical variables. The odds ratio (OR) will be the measure used to estimate risk. The OR’s significance will be evaluated by the OR’s asymptotic confidence interval. The hypothesis of normality will be verified by the Kolmogorov–Smirnov and Shapiro–Wilk tests. Student’s t-test or Mann-Whitney test will be used in the comparison of the two independent groups. More than two independent groups will be compared by the ANOVA or by the Kruskal–Wallis test. Two repeated measures in different assessments will be compared by the paired Student’s t-test or by the Wilcoxon’s signed-rank test. More than two repeated measures will be compared by the ANOVA for repeated measures, or by the Friedman’s test.

The identification of an optimal cutoff point for the marker associated with an outcome will be established through the analysis of the receiver operating characteristic (ROC) curve. The performance will be evaluated by the area under the ROC curve (AUC), and the significance of the AUC will be evaluated by the test that judges the null hypothesis that AUC is equal to 0.5. In addition to the significance test, the asymptotic confidence interval for the AUC will be obtained.

Analysis of the association between two quantitative variables will be visualized by scatter plots and quantified by the Pearson correlation coefficient, in the case of normal distributions, or by the Spearman’s correlation coefficient, if normal distribution is not verified in at least one of the variables. The significance of the correlation coefficient will be evaluated by the correlation coefficient test.

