Linear or non-linear regression models will be proposed to explain the relationship between the clinical–radiological variables of the patient and the quantitative outcome variables (colonization and multiomic profile). For the variable colonization (binary), logistic regression models will be proposed. Regression model parameters will be estimated by the maximum likelihood method, and the forward Wald method will be used to choose the variables. The goodness of fit of the model will be analyzed by adherence statistics, residual analysis, and verification of theoretical assumptions of the model.

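### BMI is listed only in four bands for the confounder analysis; if these enter the models as categories, BMI is less likely to be kept in the adjusted associations

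*Protocol article*

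**What the plan says.** The Confounding variables section introduces its list with "Below are the confounding variables to be analyzed" and gives BMI as "Underweight (< 18.5 Kg/m^2^)Normal (18.5–25 Kg/m^2^)Overweight (25–30 Kg/m^2^)Obese (> 30 Kg/m^2". No continuous form of BMI is mentioned. Age appears without bands.

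Under Statistical analysis methodology, the outcome model is "For the variable colonization (binary), logistic regression models will be proposed". On estimation and selection the text reads "Regression model parameters will be estimated by the maximum likelihood method, and the forward Wald method will be used to choose the variables". The same section judges odds ratios by their asymptotic confidence intervals and states "The inferential analysis will consider a maximum significance level of 5" per cent. It describes the predictors as the patient's clinical and radiological variables. It does not name BMI, and it does not say whether the bands enter as separate categories or as an ordered score.

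The size of the study is set for the incidence estimate alone: the minimum "for the population of interest will be 96 participants", "using a confidence interval of 95% and a maximum margin of error of 10" per cent. Recruitment continues "until 120 individuals are included, aiming at a minimum number of 96 collections".

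**The concern.** Four categories cost three regression parameters where a linear term costs one, and grouping discards the variation within each band. In a study of about 100 patients both matter. Because variables are chosen by forward selection, a confounder that is harder to detect is more often left out, and one that is left out is not adjusted for at all. The article presents control of confounding as a strength of the study, and one of its objectives is the association of colonization with clinical and radiological profile. At stake are those adjusted associations.

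A second, smaller matter is the underweight band. Few adults coming to lumbar disc surgery are likely to fall in it. If all or none of them are colonized, the maximum-likelihood odds ratio for that band is infinite or zero, and the planned asymptotic interval does not exist.

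**Working it through.** **The plan's own figure.** For a single proportion, n = z²·p(1−p)/d². With z = 1.96, p = 0.5 and d = 0.10, n = 3.8416 × 0.25 / 0.01 = 96.04, which reproduces 96. The recruitment target fits 96/(1 − 0.20) = 120, although the 20% loss is inferred, not stated. The document gives no power figure for any regression model.

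**Inputs.**
- From the document: n = 96 and 120, 5% level, the four bands, and 46% as the higher of the positive-culture rates cited in the Introduction.
- Assumed: BMI normal with mean 27 and SD 4.8; linear effect with odds ratio 1.7 per SD (1.3 as a weak alternative); 20% colonized as a lower scenario.

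**Size of the bands.** The limits 18.5, 25 and 30 lie at (18.5 − 27)/4.8 = −1.77, −0.42 and 0.625 SD. The bands then hold 3.8%, 30.0%, 39.6% and 26.6% of patients. The underweight band is expected to hold 0.038 × 96 = 3.7 patients, or 0.038 × 120 = 4.6.

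**Information kept.** The band means are −2.17, −0.94, 0.10 and 1.23 SD. The between-band variance is the sum of share × mean²: 0.181 + 0.266 + 0.004 + 0.405 = 0.86. The bands keep about 86% of the BMI variance.

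**Where the loss comes from (large-sample approximation).** A 1-df test with 80% power has noncentrality (1.96 + 0.84)² ≈ 7.85.
- The same noncentrality on 3 df gives 64% power: 16 points lost to the extra degrees of freedom.
- With about 85% of the information kept, 3-df power is 57%: a further 7 points lost to banding.

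The sparse band is not the main cause. Merging underweight with normal recovers only 0 to 5 points on the likelihood-ratio test.

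**Simulated power at n and prevalence near the plan (score test, odds ratio 1.7 per SD).**

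| n | colonized | continuous | four categories | loss |
|---|---|---|---|---|
| 96 | 20% | 53% | 26% | 27 |
| 96 | 46% | 70% | 43% | 27 |
| 120 | 20% | 61% | 32% | 29 |
| 120 | 46% | 80% | 54% | 26 |

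Repeat runs agree within about two points. The score test is used because it commonly governs entry in forward Wald procedures; the document does not say which statistic governs entry.

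**Sensitivity.**
- Weak effect (odds ratio 1.3 per SD): loss about 8 to 15 points.
- Ordered band score on 1 df, odds ratio 1.7, n = 96: 45% against 53%, and 63% against 70%; loss about 6 to 8 points.
- Across other assumed BMI distributions and effects, where the continuous term has about 40% to 90% power, the loss is roughly 15 to 33 points by likelihood ratio, 19 to 36 by score and 29 to 50 by the overall Wald test. The Wald figures are inflated by that test's conservatism: with no BMI effect, the banded version rejects only 0.5% to 2.1% of the time.

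**Underweight odds ratio.** At odds ratio 1.7 the band is empty, or has all or none of its patients colonized, in roughly 40% to 78% of simulated studies. The figure is worst at 20% colonized.

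**Effect on confounding.** Take an exposure with no true effect, assumed 40% prevalent, with BMI related to both exposure and colonization at odds ratio 1.7 per SD. The spurious exposure odds ratio is 1.27 to 1.28 with BMI omitted, 1.04 with the bands and 0.99 to 1.00 with continuous BMI.

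**The case against.** The strongest reply is that the decisive step is not written. The article lists confounders with their data categories and says that logistic models will be proposed. Dummy coding, and BMI's place in the colonization model, are readings. An ordered score would cost one parameter and lose only 6 to 8 points. Coding detail may also sit in an analysis plan that is not shown. This stands as a limit on the size of the point. It does not remove it, because the article does fix the bands and offers no continuous form.

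Second, BMI is a confounder and no objective tests it, so power for BMI is not itself a study goal. That is correct. Power matters here only because selection decides whether BMI is adjusted for. A reader might infer serious residual confounding within the wide bands. The check above does not support this: when banded BMI is kept, the spurious odds ratio is 1.04, small beside sampling error at n = 96.

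Third, a reader might take the nearly empty band as the main cause of the loss. It is not. With a right-skewed BMI distribution that band would hold about two patients, or fewer than one, of 96. If it is empty it drops out and costs no parameter. When it is sparse, it mainly spoils its own odds ratio and weakens the Wald test.

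Fourth, the simulations assume a linear truth, which favours a linear term; threshold and U-shaped effects were not tried, and standard BMI categories are a defensible descriptive choice. This stands, and is why a linearity check belongs in the fix. Finally, the plan recruits 120 and revises the sample size at the halfway point. At n = 120 the loss is about the same.

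**Conclusion.** The point holds in a limited form. The article fixes four bands for a continuous confounder. If they enter as categories, up to three parameters are spent instead of one, and most of the resulting power loss comes from those extra degrees of freedom and from the banding. The loss is about 25 to 30 points on the score test for a moderate linear effect, under the assumed BMI distribution and 20% to 46% colonized. It is about 8 to 15 points for a weak effect and about 6 to 8 for an ordered score. A reader might infer a fixed loss of 20 to 40 points, but the documents cannot support one: they give neither a BMI distribution nor an expected effect, and the incidence is what the study sets out to learn.

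The main risk is that BMI is dropped from the adjusted association models. The underweight odds ratio and its interval would also often not be estimable. The primary incidence estimate is not affected. This is a cheap improvement, not a flaw that endangers the study.

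**What to change.** State that BMI in kg/m² enters the regression models as one continuous term, and that colonized and non-colonized patients are compared on BMI as a continuous variable. Check linearity with a quadratic term. Keep the four bands for descriptive tables only.

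The cost is a sentence or two. No new data are needed, because height and weight are already required to assign the bands. The small downside is that a linear shape is assumed, which the quadratic check addresses.

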## Statistical planning

### Sample size calculation

Considering the main outcome proposed, the identification of disc colonization by *C*. *acnes*, the minimum sample size (*n*) for the population of interest will be 96 participants, according to the calculation described by Medronho et al., [59] using a confidence interval of 95% and a maximum margin of error of 10%.

The ideal sample size for analysis of secondary outcomes will depend on the incidence of the main outcome. If it is too low, an increase in the number of patients included will be performed with the inclusion of more blocks of participants. In order to have a more accurate dimension, the sample size calculation will be revised as soon as we reach half of the initially planned sample size.

### Statistical analysis methodology

The database will be analyzed using the SPSS software, version 22.0, and R software, version 4.0.2. Descriptive analysis will be performed by charts and descriptive statistics. The inferential analysis will consider a maximum significance level of 5%. The chi-square test or Fisher’s exact test will be used for inferential analysis of the distributions of categorical variables. The odds ratio (OR) will be the measure used to estimate risk. The OR’s significance will be evaluated by the OR’s asymptotic confidence interval. The hypothesis of normality will be verified by the Kolmogorov–Smirnov and Shapiro–Wilk tests. Student’s t-test or Mann-Whitney test will be used in the comparison of the two independent groups. More than two independent groups will be compared by the ANOVA or by the Kruskal–Wallis test. Two repeated measures in different assessments will be compared by the paired Student’s t-test or by the Wilcoxon’s signed-rank test. More than two repeated measures will be compared by the ANOVA for repeated measures, or by the Friedman’s test.

The identification of an optimal cutoff point for the marker associated with an outcome will be established through the analysis of the receiver operating characteristic (ROC) curve. The performance will be evaluated by the area under the ROC curve (AUC), and the significance of the AUC will be evaluated by the test that judges the null hypothesis that AUC is equal to 0.5. In addition to the significance test, the asymptotic confidence interval for the AUC will be obtained.

Analysis of the association between two quantitative variables will be visualized by scatter plots and quantified by the Pearson correlation coefficient, in the case of normal distributions, or by the Spearman’s correlation coefficient, if normal distribution is not verified in at least one of the variables. The significance of the correlation coefficient will be evaluated by the correlation coefficient test.

Linear or non-linear regression models will be proposed to explain the relationship between the clinical–radiological variables of the patient and the quantitative outcome variables (colonization and multiomic profile). For the variable colonization (binary), logistic regression models will be proposed. Regression model parameters will be estimated by the maximum likelihood method, and the forward Wald method will be used to choose the variables. The goodness of fit of the model will be analyzed by adherence statistics, residual analysis, and verification of theoretical assumptions of the model.

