### Host multiomic characteristics

Proteomic and metabolomic techniques will be used to examine disc and plasma samples. The comparison of the group of molecules found in disc and plasma samples may contribute to the quantitative and qualitative identification of profiles using peripheral blood that are associated with the presence of the pathogen in the intervertebral disc. After processing the multiomic raw data using proper bioinformatics tools, statistical techniques will be applied to analyze them against the clinical–radiological and microbiological profiles of the participants. We expect to provide a molecular signature relating the presence of *C*. *acnes*, LDD and LBP.

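### For the multiomic and marker analyses, the stated AUC test and optimal cut-off come from one cohort with no multiplicity control or validation named, so a screened marker's performance would be overstated

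*Protocol article*

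**What the plan says.** All references are to the protocol article.

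- **Level.** Statistical analysis methodology: "The inferential analysis will consider a maximum significance level of 5" per cent. No family of tests and no adjustment is named.
- **Cut-off.** Same section: "The identification of an optimal cutoff point for the marker associated with an outcome will be established" from the ROC curve. The marker is not identified.
- **AUC.** Same section: "the significance of the AUC will be evaluated by the test that judges the null hypothesis that AUC is equal to 0.5", with an asymptotic interval in addition.
- **Regression.** The end of that section lists the multiomic profile, with colonization, among the outcome variables to be modelled, and chooses variables by forward Wald.
- **Aim.** Host multiomic characteristics looks for peripheral-blood profiles associated with the pathogen in the disc and states "We expect to provide a molecular signature relating the presence of" *C. acnes*, LDD and LBP. The fourth item under Hypotheses and objectives is the same aim. The statistics for the multiomic data are otherwise left open.
- **Cohort and size.** Patient and public involvement: recruitment runs "until 120 individuals are included, aiming at a minimum number of 96 collections". The 96 comes from a precision calculation "using a confidence interval of 95% and a maximum margin of error of 10" per cent. For everything else, "The ideal sample size for analysis of secondary outcomes will depend on the incidence of the main outcome".

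No section mentions false discovery rate control, cross-validation, bootstrap correction, a hold-out set or an external cohort.

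**The concern.** Proteomics and metabolomics produce many candidate features from few patients. A test of AUC = 0.5 and its large-sample interval are valid for a marker fixed before the data are seen. They are not valid for the best of many candidates judged in the patients who selected it, because the maximum of many noise AUCs lies well above 0.5.

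A second problem is separate from this. An optimal cut-off chosen and evaluated in the same patients overstates sensitivity and specificity, even when there is only one marker and it was named in advance.

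At stake is objective 4. A molecular profile of colonized patients could be reported with spurious members and with an accuracy that would not recur in new patients.

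**Working it through.** **1. The plan's own figure.** n = 1.96² × p(1 − p) / d². With d = 0.10 from the protocol and p = 0.5 assumed (the protocol gives no expected proportion), n = 3.8416 × 0.25 / 0.01 = 96.04, so the stated 96 reproduces. It is a precision calculation for one proportion and says nothing about marker discovery.

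**2. Inputs that must be assumed.** The protocol does not give the number of features; 20 to 1,000 independent features with no signal are used. It gives no expected colonization rate either. The Introduction cites 46% positive for anaerobes in one series, and 0.46 × 96 ≈ 44. It cites 3.4% of discs in another, and 0.034 × 96 ≈ 3 if applied per patient. Rates of 20% (19 patients) and 10% (10 patients) are assumed intermediate values. All 96 patients are assumed to enter the multiomic analysis.

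**3. False positives at 5% per test.** The chance of at least one is 1 − 0.95^m:

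- m = 20: 1 − 0.95^20 = 64.2%, with 20 × 0.05 = 1 expected
- m = 100: 1 − 0.95^100 = 99.4%, with 100 × 0.05 = 5 expected
- m = 1,000: practically 100%, with 1,000 × 0.05 = 50 expected

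**4. Spread of a noise AUC.** Null SD = √[97 / (12 × n1 × n2)], with n1 colonized and n2 = 96 − n1:

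- 44 and 52: √(97 / 27,456) = 0.059
- 19 and 77: √(97 / 17,556) = 0.074
- 10 and 86: √(97 / 10,320) = 0.097

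**5. Best noise feature, simulated (mean apparent AUC).**

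| Colonized | m = 100 | m = 500 | m = 1,000 | Sensitivity / specificity at the optimal cut-off, m = 1,000 |
|---|---|---|---|---|
| 44 | 0.66 | 0.69 | 0.70 | 0.69 / 0.69 |
| 19 | 0.70 | 0.74 | 0.75 | 0.78 / 0.67 |
| 10 | 0.76 | 0.80 | 0.82 | 0.87 / 0.73 |

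A second simulation at m = 1,000 gave 0.71, 0.75 and 0.82. In every cell of the table the asymptotic interval excluded 0.5 in more than 99% of runs. In new noise patients the AUC was about 0.50, and sensitivity + specificity − 1 was about 0.

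**6. A score instead of one marker.** Combining the top five noise features (m = 100 to 1,000) gave apparent AUCs of 0.78–0.85 with 44 colonized, 0.83–0.90 with 19 and 0.90–0.96 with 10. In new patients they were 0.49–0.51.

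**7. One prespecified marker (m = 1).** The AUC test rejected in 4.3% to 5.3% of runs, as it should. The optimal cut-off still looked informative on noise. With 19 colonized, sensitivity was 0.64 and specificity 0.57, so their sum minus 1 was 0.21 against a true value of 0. In this run the marker's direction was also read from the data.

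**8. Effect of correction.** For m = 20 to 1,000, Benjamini-Hochberg at 5% left a chance of any significant noise feature of 0.7% to 5.1%.

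**The case against.** The strongest reply is that much of this rests on silence. The document is a journal article, its analysis plan is not shown, and false discovery rate control or internal validation may be specified there. Several stronger readings are tempting, and the text does not support them:

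- **That all inference is uncorrected at 5%.** The article sets a maximum level and does not say that adjustment will be omitted. The primary outcome is one proportion with a 95% interval, which multiplicity does not touch.
- **That every protein and metabolite is tested at 5%.** The Proteomics section describes identification, validation and comparison software but no test per protein. The Metabolomics section names software without a threshold.
- **That the ROC marker is certainly chosen from the multiomic data.** The text speaks of a marker in the singular and does not link it to a screening step. With one marker named beforehand, the AUC test would be sound.
- **That choosing a cut-off invalidates the AUC test.** It does not. The AUC is taken over all thresholds, so only selection of the marker distorts the test and interval. Selection of the cut-off distorts sensitivity and specificity.

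The sizes are also conditional. The feature count, the independence of features and the 19 and 10 colonized patients are assumptions. With 44 colonized, a best single noise marker at about 0.70 is significant but modest.

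All of this stands and sets the limits of the point. It does not remove the point, because the article itself fixes the AUC criterion, the interval and the cut-off rule. The same section brings the multiomic profile within its scope, and no marker is named anywhere. An analysis plan would have to override these rules as well as fill a gap.

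**Conclusion.** The point holds, limited to the multiomic and marker analyses behind objective 4. It has an unconditional part and a conditional part.

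- **Unconditional.** Sensitivity and specificity at a cut-off optimized in the same patients are optimistic, even for a prespecified marker.
- **Conditional.** If the marker is selected from the proteomic or metabolomic features, which is the most natural reading of the signature aim but still an inference, the AUC = 0.5 test and its interval are invalid. A significant result is then close to certain on noise once about 100 independent features are screened.

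How convincing the noise looks grows with the number of features and as the number of colonized patients falls. Correlation between features would reduce it. The matter should be settled before the multiomic data are analysed; it is no reason to doubt the primary estimate.

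**What to change.** Add to Statistical analysis methodology, or to the analysis plan with a statement that it governs:

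1. Control the false discovery rate across features within each platform and specimen type, for example by Benjamini-Hochberg at 5%.
2. Report AUC, sensitivity and specificity from cross-validation or an optimism-corrected bootstrap, with feature selection and cut-off selection repeated inside each resample.
3. Keep the plain test of AUC = 0.5 for markers named before the data are seen, and list those markers.
4. Label the signature as discovery that needs external validation. If too few patients are colonized for resampling (about 3 of 96 at the lower cited rate), report it as purely descriptive.

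Benjamini-Hochberg is one reasonable choice among several; what matters is that some control is stated in advance. The cost is some loss of power, so fewer features are declared significant, together with lower reported AUCs and some computing time. No extra patients or samples are needed.
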